# Effect of 12-week head-down strong abdominal breathing on cognitive function in patients with stable chronic obstructive pulmonary disease: a single-centre randomised controlled trial protocol

**DOI:** 10.1186/s13063-024-08193-8

**Published:** 2024-05-30

**Keywords:** Abdominal breathing, Cognition, Ba Duan Jin, COPD, Rehabilitation training

## Abstract

**Background:**

Patients with chronic obstructive pulmonary disease (COPD) often suffer from a combination of mild cognitive impairment (MCI) and a significant reduction in their quality of life. In the exercise programme of pulmonary rehabilitation (PR), pulmonary rehabilitation intervention is often carried out by enhancing respiratory function. Strong abdominal breathing is a kind of breathing method, through which the diaphragm can be exercised, thereby enhancing the deflection distance of the diaphragm during breathing and improving respiratory function. The inversion trainer can meet the different angles of head-down training and also has the characteristics of low cost, easy to operate, and use a wide range of scenarios. According to currently available data, strong abdominal breathing in combination with head-down position has not yet been used in pulmonary rehabilitation in this type of rehabilitation programme. It is valuable to use this device to study PR of cognitive function in patients with COPD.

**Methods:**

This study was a 12-week single-centre randomised controlled trial and blinding the assessors and data processors of the test. Recruitment is planned for January 1, 2024. It is expected that 81 patients with stable COPD combined with MCI will be recruited and randomly assigned to the head-down strong abdominal breathing group (HG), the fitness qigong eight-duanjin group (BDJ), and the control group (CG) in a 1:1:1 ratio. Using fNIRS (functional near-infrared spectroscopy) to assess brain oxygen availability before and after pulmonary rehabilitation in three periods: before, during and after the intervention. Cognitive functioning is also assessed using the Overall Cognitive Assessment Scale, the Specific Cognitive Functioning Assessment Scale and the Cognitive Behavioural Ability Test.

**Trial registration:**

The Specialised Committee on Scientific Research and Academic Ethics of the Academic Committee of Anqing Normal University approved the project (ANU2023001). China Clinical Trial Registry approved the study (ChiCTR2300075400) with a registration date of 2023/09/04.

**Discussion:**

The aim of this study was to explore novel exercise rehabilitation methods to improve cognitive function in COPD patients. It results in a lower financial burden and higher participation in pulmonary rehabilitation and improves the quality of survival of patients with COPD.

**Supplementary Information:**

The online version contains supplementary material available at 10.1186/s13063-024-08193-8.

## Introduction

Chronic obstructive pulmonary disease (COPD) is a common preventable and treatable chronic disease characterised by airway obstruction, which is caused by exposure to inhaled particulate matter (e.g. cigarette smoke and air pollutants) as well as genetic, developmental and social factors [1]. In patients with chronic pulmonary obstructive disease, as the disease progresses, stiffness of the soft tissues and joints in the neck and shoulders restricts physical movement, including head extension, high tension in the neck muscles [2], thoracic kyphosis and internal rotation of the shoulders, the contractile properties of the diaphragm fibres are diminished, elasticity is reduced, series of muscle segments are absent, myofibrillar proteins are destroyed and the diaphragm morphology is altered [3]. The diaphragm is an important respiratory muscle for maintaining respiratory ventilation. The mechanical effects caused by systemic inflammation and hyperinflation can lead to diaphragmatic dysfunction in patients with COPD [4]. These changes put the diaphragm at a mechanical disadvantage, resulting in a reduced ability of the diaphragm to generate flow and pressure, increasing respiratory work and leading to diaphragmatic fatigue [5]. Moreover, these changes can cause chest tightness, inspiratory muscle weakness, increased respiratory resistance, severe breathing difficulties and even affect physical activity and the ability to walk [6]. Also, patients with COPD often have comorbid MCI and a higher prevalence of cognitive impairment (range 10–61%, mean 36%) than the normal population (range 5–24%, mean 12%) [7]. It is usually characterised by frequent memory loss, functional disability, poor physical and mental health and rapid decline in cognitive function over time [8]. The aetiology of cognitive impairment in COPD patients is multifactorial, such as lung inflammation (elevated C-reactive protein levels), and hypoxaemia [9, 10].

Although cognitive dysfunction is associated with quality of life and rehabilitation outcomes in COPD patients [11, 12], it has attracted the attention of experts and scholars in the field. However, cognitive rehabilitation therapy for COPD patients is still in the exploratory stage internationally. Currently, VR-based technology combined with health education [13], cognitive therapy based on mindfulness-based therapy [14], pulmonary rehabilitation combined with cognitive training [15], long-term oxygen therapy [16], and lung volume reduction surgery have been applied in the cognitive rehabilitation process of COPD patients [17] and have significant effects. If we look at the ease, economy, and flexibility of implementing cognitive rehabilitation therapy, it seems that the exercise approach through rehabilitation at home or in the community is a good choice. However, the variety of exercise rehabilitation therapies to improve cognitive function in COPD patients needs to be further enriched, so as to provide patients with more diversified choices of exercise rehabilitation programmes.

With the advent of inversion devices in rehabilitation, more and more people are using such devices for rehabilitation. In a study of head-down training in an elderly population, it was shown that changes in body position had an effect on cerebral blood flow and also led to a reduction in psychological stress and improved sleep quality in the lives of older people [18]. In another study on the magnitude of diaphragmatic excursions in healthy subjects, the optimal change in diaphragmatic excursions was obtained in healthy subjects using a 30° head-down tilt position [19]. Strong abdominal breathing is one type of breathing. Currently, studies exploring MCI in COPD patients through head-down strong abdominal breathing training are rare internationally. Previous studies have found that head-down training has a relatively significant effect on, for example, cerebrovascular function [18], while studies of lung function have found heterogeneity. A review of the relevant literature also revealed that respiratory training can improve cognitive function in COPD patients [20], but the depth of research needs to be further improved. Therefore, this study will explore the cerebral blood flow alteration status through head-down strong abdominal breathing training. We also monitored the status of HbO2 changes in the prefrontal cortex by fNIRS and evaluated the improvement of cognitive function in COPD from multiple perspectives by combining the Overall Cognitive Assessment Scale, the Specific Cognitive Assessment Scale, and the Cognitive Behavioural Ability Level Test [21–23].

The effectiveness of traditional Chinese sports in promoting health is well documented. In particular, the Eight Duan Jin exercises have been shown to improve the respiratory function of the body, mainly by enhancing the elasticity of the diaphragm and increasing the volume of the thorax, thereby increasing the inspiratory volume of the lungs and improving exercise capacity [24, 25]. We compared Fitness Qigong Ba Duan Jin with head-down strong abdominal breathing to verify the effectiveness of head-down strong abdominal breathing in relation to traditional Chinese exercise programmes in improving cognitive function in COPD patients.

The design of this study takes into account the significance and value of the practical application of multiple aspects of the study. Firstly, from the patient’s point of view, COPD patients suffer from a range of personal, family and social problems caused by cognitive dysfunction. For example, it reduces the quality of patients’ survival and imposes a huge economic burden on their families and society [26]. Secondly, from the perspective of researchers in related fields, exploring the rehabilitation effect of cognitive function in COPD patients through the exercise rehabilitation of head-down strong abdominal breathing may have a certain reference and borrowing value, so as to facilitate related professionals to explore more scientific and efficient exercise rehabilitation therapies. Finally, from a health system perspective, this study has a relatively large population and scope of application and can be intervened in the home, the community, and in outpatient settings. It may be possible to alleviate some of the pressure on the health care system.

## Research methodology

### Design

This study was a single-centre randomised controlled study with three measurement periods (One week before the experiment, week 6 of the experiment and the first week after the experiment.). Assessors for cognitive and physical tests and data analysts are formally blinded, while participants and trainers are unblinded. Eighty-one COPD patients (GOLD I-II) will be recruited for this study and randomly assigned in a 1:1:1 ratio to the HG, BDJ and CG groups, with the HG and BDJ groups receiving a 12-week motor rehabilitation intervention. The availability of oxygen in the dorsolateral prefrontal cortex (PFC) was monitored by fNIRS at all times during the cognitive task, and cognitive function was assessed in conjunction with relevant cognitive scales. To explore the improvement of cognitive function in COPD patients by strong abdominal breathing in a head-down position. This study design and participant flow is shown in Fig. 1, and the relevant demographic and baseline data indicators to be measured are shown in Table 1. For the study duration and SPIRIT checklist, please see the Additional file.

**Fig. 1 Fig1:**
[figure not shown]
Flowchart of the design of experiments

**Table 1 Tab1:** Demographic and baseline characteristics

Characteristics	HG (*n* =)	BDJ (*n* =)	CG (*n* =)	*P* value
Women, *n* (%)	x	x	x	x
Age, years, ± SD	x	x	x	x
BMI, kg m^2^	x	x	x	x
FEV1, %pred	x	x	x	x
FVC, %pred	x	x	x	x
PaO_2_, mmHg	x	x	x	x
PaCO_2_, mmHg	x	x	x	x
SPO_2_, %	x	x	x	x
GOLD Stage I	x	x	x	x
GOLD Stage II	x	x	x	x
TSI, index	x	x	x	x
SGRQ, score	x	x	x	x
MMRC, index	x	x	x	x
MIP, cmH2O	x	x	x	x
MEP, cmH2O	x	x	x	x
CAT, score	x	x	x	x
6MWD, m	x	x	x	x
Overall cognitive function				
MoCA, score	x	x	x	x
Stroop, index	x	x	x	x
ACE-R, score	x	x	x	x
MMSE, score	x	x	x	x
Specific cognitive functions				
TMT-A, score	x	x	x	x
TMT-B, score	x	x	x	x
Digital breadth test DST, score	x	x	x	x
VFT language fluency test, score	x	x	x	x
Berg Balance Scale (BBS), score	x	x	x	x
Eliminate test, score	x	x	x	x
Cognitive behavioural assessment				
PCI, score	x	x	x	x
TUGT, s	x	x	x	x
30-m pace, m/s	x	x	x	x
30-m walking time, s	x	x	x	x
30-m cadence, steps/min	x	x	x	x

Data are mean ± SD unless specified otherwise. Level of significance was set at *P* ≤ 0.05

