### Sample size

The sample size is determined primarily on the basis of the key outcome indicators of the trial. The sample size was calculated by applying ANOVA with G-power (3.1.9.7) software, where the effect size was 0.25, *α* was 0.05 and power was 0.8, resulting in a calculated sample size of 69. Considering that there might be 10–15% sample attrition, we planned to invite 81 COPD patients to participate in the trial.

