### Statistical analysis

All statistical analyses were performed using SPSS v.27.0. Data are presented as means and standard deviations or proportions. Standard error of the mean (± SEM) was used to look at trends between cardiorespiratory and cerebrovascular changes during exercise and was more appropriate than SD, which was used to indicate the variability of data between patients. Statistical significance of differences between groups was assessed by analysis of variance, paired *t*-test and chi-square test. In addition, one-way ANOVA with repeated measures was used to determine statistically significant differences between the different percentiles of total exercise duration for oxy-Hb, Deoxy-Hb, Total-Hb, TSI, and blood oxygen saturation during exercise. Multiple comparisons using LSD honestly significant difference post hoc procedure to determine pairwise differences. Pearson’s correlation coefficient was used to assess the bivariate relationship. Multiple linear regression models were used to assess potential relationships between determinants of cognitive impairment and changes in cerebral oxygen utilisation and cerebral haemoglobin volume. Missing values in the data will be statistically analysed by multiple interpolation. The level of bivariate significance was set at *P* ≤ 0.05.

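### Table 1 plans a test at P ≤ 0.05 on all 32 baseline rows across randomised arms; these P values do not show which imbalances matter, and the column should go (minor)

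*Protocol article*

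**What the plan says.** The Design section of the protocol article states "Eighty-one COPD patients (GOLD I-II) will be recruited for this study and randomly assigned in a 1:1:1 ratio" and that "the relevant demographic and baseline data indicators to be measured are shown in Table 1". Table 1 is titled "Demographic and baseline characteristics". Its columns are HG, BDJ, CG and P value. All 32 data rows carry a placeholder in the P value column; only the three sub-heading rows are blank. The footnote reads "Data are mean ± SD unless specified otherwise. Level of significance was set at" P ≤ 0.05.

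The Statistical analysis section says "Statistical significance of differences between groups was assessed by analysis of variance, paired" t-test and chi-square test, and sets the same 0.05 level. It names no baseline covariate for the comparison between arms. Its multiple regression concerns determinants of cognitive impairment, not the treatment effect.

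The Randomisation and blinding section lets a patient who cannot accept the allocated arm for a medical reason move to another arm, and leaves that patient's data out of the analysis. No section withdraws the P value column or says what the baseline P values are for.

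**The concern.** A significance test asks whether a difference could have arisen by chance. Between arms formed by randomisation, that is how baseline differences do arise, so the answer is known in advance. Whether an imbalance matters depends on its size and on how strongly the variable predicts the outcome. A P value measures neither.

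The column can mislead in two directions. A row that reaches 0.05 by chance may prompt doubt about the allocation. A row that misses 0.05 may be taken to show that the arms are comparable, although the imbalance is large enough to shift the result. The second matters more here: the main outcome, the prefrontal tissue oxygen saturation index (TSI), and the cognitive scores MoCA, ACE-R and MMSE are all rows of Table 1, and the stated between-group methods include no adjustment for their baseline values.

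**Working it through.** The plan gives no figure of its own for the baseline tests, so there is none to reproduce.

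**Inputs**
- Rows with a P value cell in Table 1, counted: 10 from sex to GOLD stage II, 7 from TSI to 6MWD, 4 overall cognitive, 6 specific cognitive, 5 cognitive behavioural. Total 32.
- Level: 0.05 (Table 1 footnote).
- Patients per arm: 81 / 3 = 27 (Design).
- Correlation between rows: not given. Assumed range 0 to 0.7, equal for all pairs.

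**1. Chance flags**

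Expected number = 32 × 0.05 = 1.6. This does not depend on the correlation between rows.

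Probability of at least one flag if the rows were independent: 1 − 0.95^32 = 0.806.

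The rows are not independent. GOLD I and GOLD II are complements, 30-m pace and walking time carry nearly the same information, and the global cognitive scales overlap. A simulation of 32 equally correlated normal variables, three arms of 27, with a one-way F test on each, gave:

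| Assumed correlation | Probability of at least one flag |
|---|---|
| 0 | 0.81 |
| 0.3 | 0.67 |
| 0.5 | 0.54 |
| 0.7 | 0.35 |

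The mean number of flags stayed between 1.5 and 1.6 throughout. Counting GOLD stage once gives 31 × 0.05 = 1.55 and 1 − 0.95^31 = 0.796, which changes nothing.

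**2. Imbalances passed over**

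Suppose one arm's observed mean lies d SD from two equal arm means. The deviations from the overall mean are 2d/3, −d/3 and −d/3, and their squares sum to 2d²/3. With n per arm:

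F = n × (2d²/3) / 2 = n d²/3, on 2 and 3n − 3 degrees of freedom.

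For n = 27 this is F = 9d² on 2 and 78.
- At d = 0.5: F = 9 × 0.25 = 2.25. With 2 numerator degrees of freedom, P = (1 + 2F/78)^(−39) = (1.0577)^(−39) = 0.11. Not flagged.
- The 5% critical value is 3.11, so a flag needs d = √(3.11 / 9) = 0.59 SD.

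If Table 1 described only the 69 patients of the sample-size calculation, 23 per arm, the threshold would rise: critical value 3.14, d = √(3 × 3.14 / 23) = 0.64 SD.

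**The case against.** The strongest reply is that nothing depends on the column. The protocol does not use baseline P values to choose covariates, exclude patients, judge the randomisation or change a model. A misreading of the table is a forecast about readers, not something the text instructs. This stands, and it sets the weight of the point.

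The protocol article also leaves room for a separate analysis plan, so the lack of named covariates is not in itself a fault. That stands too. But a P value column with a stated threshold is a positive choice, not an omission, so that reply does not cover it.

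A third reply is that baseline differences need not be pure chance here, because patients who change arm are dropped from the analysis. If Table 1 describes the analysed set, which is not stated, this is right for those patients. It does not rescue the column: the document gives it no checking purpose, and reporting transfers and exclusions by arm would show the problem directly.

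Some stronger readings are tempting but not supported:
- **The table is certain to show false imbalances.** The figure of 1.6 is an expectation. On the assumed correlations, the chance of no flag at all is about 19% to 65%.
- **81% is the figure to quote.** It holds only if the 32 rows are independent, which they are not.
- **The fault can be stated as low power to detect a shift.** Power refers to a true difference between populations, which randomisation rules out. The relevant quantity is the P value attached to an observed imbalance, as in step 2.
- **GOLD stage is tested twice.** Two filled cells in an empty table shell do not establish that; one chi-square test could fill both.

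**Conclusion.** The point holds as a minor flaw of reporting and interpretation. Table 1 plans 32 baseline tests at 0.05 across randomised arms. About 1.6 chance flags are expected, with a 35% to 81% probability of at least one for assumed correlations from 0.7 to 0. At 27 per arm, one arm has to sit about 0.59 SD from two equal arms before the F test flags it, so a half-SD imbalance in baseline TSI or MoCA would be printed as not significant (P = 0.11).

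A reader might infer that the baseline tests bias the primary comparison or steer the choice of model. The document does not support that, since no decision is attached to them.

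The figures assume approximately normal variables, a one-way F test on each row (a simplification for the categorical rows), 27 patients per arm, and differences that arise by chance apart from patients dropped after a transfer.

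**What to change.** 1. Remove the P value column and the significance sentence from the Table 1 footnote. Report mean (SD) or n (%) by arm.
2. In Statistical analysis, replace the unadjusted between-group comparison with one adjusted for the baseline value of the outcome being analysed: TSI for the main outcome, and each cognitive score for its own analysis. Specify this in advance and apply it whatever the baseline table shows.

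The second change is an improvement to a stated method, and it deals directly with the imbalance that the P value column cannot judge. Both changes use data already planned for collection. The cost is one deleted column, an edited footnote, a revised sentence in the analysis section and one covariate per model.

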### Patient and public involvement

No patients/public were involved in the design, implementation, reporting or dissemination plans for our study.

### Organisation and supervision of the experiment

An Experimental Research Validation Team (ERV) was established prior to the start of the experiment. The main members are the designer of this experimental study, the project leader, the chief physician of the Department of Respiratory Medicine, Anqing Hospital of the People’s Liberation Army Navy, and the data analyst. A seminar is held every Friday, focusing on the optimisation of the experimental protocol. At the same time, an Experimental Steering Committee (ESC) will be established. Primarily responsible for pre-lab training, professional guidance and supervision of patients during labs. Among them, the experimental supervisors mainly included professional master’s degree students in sports training, rehabilitation therapists, and outpatient doctors from the respiratory department of the Naval Hospital Anqing. Experimental supervisors included the project leader and the chief physician of the Respiratory Department of the Naval Anqing Hospital. The Experimental Steering Committee will meet fortnightly. Discusses primarily the status of the implementation of the research protocol within the scope of the experimental phase. Includes problems encountered during experimental guidance, problems identified by experimental supervisors, and patient feedback to experimental staff. And to answer and optimise the corresponding questions, so that this study can be completed scientifically, rationally and smoothly.

### Sample size

The sample size is determined primarily on the basis of the key outcome indicators of the trial. The sample size was calculated by applying ANOVA with G-power (3.1.9.7) software, where the effect size was 0.25, *α* was 0.05 and power was 0.8, resulting in a calculated sample size of 69. Considering that there might be 10–15% sample attrition, we planned to invite 81 COPD patients to participate in the trial.

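### The 80% power claimed for N = 69 does not hold for the between-group analysis of variance in the analysis section, and the group-by-time test that reproduces 69 is not named there

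*Protocol article*

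**What the plan says.** The protocol article's Sample size section gives the method and effect size: "The sample size was calculated by applying ANOVA with G-power (3.1.9.7) software, where the effect size was 0.25". It sets alpha at 0.05 and goes on that "power was 0.8, resulting in a calculated sample size of 69". The attrition step follows: "Considering that there might be 10–15% sample attrition, we planned to invite 81 COPD patients to participate in the trial". The section does not give the type of ANOVA, the number of groups or measurements, a correlation between visits or a sphericity value.

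The Design section fixes three arms, with patients "randomly assigned in a 1:1:1 ratio to the HG, BDJ and CG groups", and three measurement periods: the week before, week 6 and the first week after. Main results makes the TSI the primary measure.

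For comparing arms, the Statistical analysis section says: "Statistical significance of differences between groups was assessed by analysis of variance", together with a paired t-test and a chi-square test. The only repeated-measures ANOVA it names is a one-way analysis across percentiles of exercise duration within a session. No group-by-time term appears.

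**The concern.** A sample size supports a trial only through the test it was computed for. Here the sample size section says ANOVA and the analysis section says analysis of variance for group differences, so a reader will take the two to be the same test. For an ordinary three-group comparison at f = 0.25, 69 patients is less than half of what 80% power requires.

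The power statement is the only justification given for recruiting 81 patients. If the between-group ANOVA is the primary test, the article reports 80% power for a comparison with about an even chance of detecting the planned effect, and a non-significant result would carry much less information than the article implies. If another test was meant, the analysis section does not commit the trial to it.

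**Working it through.** **Inputs.** From Sample size: effect size 0.25 (read as Cohen's f, the ANOVA metric in the named software), alpha 0.05, target power 0.80, stated N 69, planned N 81. From Design: 3 groups at 1:1:1 and 3 measurement periods. Assumed, because not stated: the correlation between visits (rho) and sphericity (epsilon = 1). Power is the upper tail of the noncentral F distribution beyond the 5% critical value.

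**Step 1. Reproduce 69.** Take the group-by-time interaction with 3 groups and 3 visits:

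- lambda = 3 × N × f² / (1 − rho), with df 4 and 2(N − 3).
- N = 69, rho = 0: lambda = 3 × 69 × 0.0625 = 12.94, df 4 and 132, power 0.820.
- N = 66, rho = 0: lambda = 12.38, df 4 and 126, power 0.799.

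With equal groups, 69 is the smallest N that reaches 80%, so the stated figure is matched exactly. At N = 69, power for this test rises to 0.941 with rho = 0.3 and 0.989 with rho = 0.5. Zero correlation is therefore the cautious choice for it.

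A second route is the repeated-measures between-factor test, which averages over visits, with lambda = 3 × N × f² / (1 + 2 rho). It gives 69 only for rho of about 0.12 to 0.14. At rho = 0.5 it needs 108 and has power 0.598 at N = 69. The analysis section does not name this test either.

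**Step 2. The between-group ANOVA at one time point or on change scores.** lambda = N × f², with df 2 and N − 3:

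| N | lambda | Power |
|---|---|---|
| 69 | 69 × 0.0625 = 4.31 | 0.426 |
| 81 | 81 × 0.0625 = 5.06 | 0.493 |
| 156 | 156 × 0.0625 = 9.75 | 0.797 |
| 159 | 159 × 0.0625 = 9.94 | 0.805 |

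Eighty per cent power therefore needs 159 patients (53 per arm). The f detectable with 80% power is about 0.38 at N = 69 and 0.35 at N = 81.

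**Step 3. Baseline adjustment, which the article does not mention.** For ANCOVA with baseline correlation r, lambda = N × f² / (1 − r²), with df 2 and N − 4, taking f on the unadjusted scale:

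| r (assumed) | Power at N = 69 | Power at N = 81 |
|---|---|---|
| 0.5 | 0.544 | 0.620 |
| 0.7 | 0.722 | 0.796 |

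**Step 4. Attrition.** 69 / 0.90 = 76.7 and 69 / 0.85 = 81.2, so 81 is consistent with the stated 10–15%. The problem lies in the 69, not in this step.

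**The case against.** The strongest reply is that 69 is not a miscalculation. It follows exactly from the trial's own three groups and three visits under a group-by-time interaction. Analysis of variance is a generic term that could cover a mixed model, and the analysis section never calls the between-group test one-way. On that reading 69 is enough at f = 0.25, and more than enough with any positive correlation between visits. This stands. A reader might infer that the software could not have returned 69, or that zero correlation is a flaw because it is unrealistic. The documents and the arithmetic support neither: 69 is reproducible, and zero correlation works against the interaction test.

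It may also be said that a condensed article leaves correlation and sphericity inputs to a full protocol or analysis plan. Their absence alone would not be a finding. What remains is that the test which yields 69 is a group-by-time test, while the analysis section describes its between-group comparison without one and uses its only repeated-measures ANOVA for something else. A document not shown could name the missing test, but it would not make these two sections agree as written.

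Finally, the underpowering is conditional. It depends on an unadjusted between-group ANOVA being primary, and baseline adjustment would narrow the gap.

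**Conclusion.** The concern holds in conditional form. The stated 80% belongs to a test that the analysis section does not contain. If the between-group analysis of variance it does name is the primary test, taken at one time point or on change scores, power at f = 0.25 is about 43% at N = 69 and 49% at N = 81, against a requirement of 159. With ANCOVA and an assumed baseline correlation of 0.5 to 0.7, power is about 54–72% at N = 69 and 62–80% at N = 81. If the group-by-time interaction was intended, power at 69 is 0.82 or better under sphericity, and the fault is only that the analysis does not name it.

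A reader might infer that the trial is too small under any analysis, or that it is bound to miss its effect. The documents do not support that, since the answer depends on which test is primary. These results assume that 0.25 is Cohen's f, equal groups and, for the interaction, sphericity.

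**What to change.** Keep 81 patients and make the two sections agree, in one of two ways.

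1. If the interaction was intended, say in Sample size that 69 comes from a repeated-measures group-by-time interaction with 3 groups, 3 visits, f = 0.25, zero correlation and sphericity. Then name that test of TSI over the three visits as the primary between-group analysis in Statistical analysis.
2. If the between-group ANOVA is primary, restate its power at f = 0.25 as about 43% (N = 69) and 49% (N = 81), with detectable f of about 0.38 and 0.35. If baseline-adjusted ANCOVA is adopted instead, give the range above together with the correlation assumed.

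Either way the cost is a reworded paragraph and, under option 1, one added sentence in the analysis section. No patients or visits are added. Under option 2 the stated power is less favourable. The choice should be made without reference to outcome data by arm.
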